### Procedures: study phase 3 (Specific Aim 4) — months 43–60

Phase 3 will use a two-group RCT (n = 160) to evaluate the effectiveness of targeted marketing versus standard clinical information in increasing parent impressions of PSQ and persuading parents of ASUDs to seek out information about EBP. Study hypotheses will be tested using the PSQ, which was adapted and validated in Phases 1–2, as well as behavioral indicators of information-seeking. Recruitment will occur using the same eligibility criteria and multimethod, single-mode approach as Phase 2.

### Sample size and power

One meta-analysis of the effect size (ES) of marketing campaigns on the proportion of customers inquiring about or purchasing a service found an average ES of .20 across 133 studies [80]. Of note, only one of the 133 studies tested marketing for a health-care service, and this study found a higher ES of .30. This ES is consistent with results of a recent quasi-experimental study comparing the effectiveness of a DTC campaign versus standard clinical guidelines in predicting cervical cancer screenings (d = .26) [81]. Assuming that awareness of the services marketed in prior studies was higher than current awareness of EBP, targeted marketing has the potential to produce larger ES in the current study. The target sample of 160 (n = 80 per group) will provide 71 percent power to detect an ES of .4; 88 percent for an ES of .5; and 96 percent for an ES of .6 [82]. Thus, the proposed sample size will be adequate to detect a medium ES, which is appropriate for a study that aims to provide proof of concept.

### Randomization

A computer-generated urn randomization procedure will be used to retain random allocation, while balancing relative probabilities of assignment to treatment groups (urns). Randomization will occur after participants complete the eligibility screening and prior to the manipulation. Variables added to the urn will include both parent (e.g., gender, race/ethnicity, parent substance use) and ASUD characteristics (e.g., number of concerns endorsed on the substance use screener, history of substance use treatment).

Parents will be randomized to one of two conditions: targeted marketing or standard clinical information. Parents in the marketing condition will be presented with the descriptions of EBP that were rated as most appealing in Phase 2, whereas parents in the standard information condition will review descriptions of EBP created for parents by leading scientific organizations in our field such as the National Institute on Drug Abuse (NIDA), Division 53 of The Society of Clinical Child and Adolescent Psychology (APA), and the Substance Abuse and Mental Health Services Administration. A sample standard clinical information message (from the APA Division 53 website) is: *Some treatment approaches have a strong backing in scientific evidence and other treatments have less evidence supporting them. Therapists who use treatments based on science use what is called “evidence-based practice…”* Messages will be balanced to ensure comparable number of words.

### Data collection and measures

The trial and quantitative data collection will be administered with Ilume software, a program designed for research surveys that is frequently used by the investigative team and that minimizes the likelihood of missing data. *Baseline*. In addition to the core set of measures, parents will answer questions assessing EBP attitudes, awareness, prior use, and intent to use (based on survey items from Phase 2). Parents will then be presented with one of two descriptions of EBP, depending on their random assignment. *Post-intervention*. Parents will complete Likert-scale ratings of the presented information in terms of its relevance to their teen/family, appeal, believability, ease of understanding, and amount of information conveyed. Parents will then complete the PSQ measure and a Behavioral Intentions Scale. After parents complete these measures, they will view a message thanking them for their participation. They will then see two links: 1) a link to end the study session, and 2) a link to receive more information about EBP service options for their teenager. The proportion of parents clicking the link to receive more information will be viewed as a secondary indicator of intentions to seek out EBP.

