**Discussion:**

The current study will inform the field whether a well-established marketing framework and measurement approach can be used to increase demand for EBP among parents of ASUDs. Results of this study will have the potential to immediately inform DTC marketing efforts by professional organizations, federal agencies, clinicians, and clinical researchers.

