### Outcomes

Descriptive statistics will be generated to describe the data. Mean comparisons will be used to test the hypothesis that participants in the marketing condition will have greater perceptions of service (as measured by the PSQ). The hypotheses that participants will report greater behavioral intentions to use EBP and will demonstrate greater likelihood to request information about EBP will be measured by group comparisons using continuous ratings on the Behavioral Intentions Scale and a categorical indicator of whether the participant actually requested information, respectively. If group differences emerge in these basic analyses, multiple regression models will test whether the group differences persist when controlling for pre-manipulation variables such as EBP attitudes, EBP awareness, intentions to seek therapy, and readability statistics generated on the messages. For all of the hypotheses, exploratory analyses will be conducted to evaluate potential moderators and mediators. Ethnicity/race, gender, and treatment history will be tested as potential moderators of group differences, and ratings of the information (e.g., ease of understanding, believability) will be tested as potential mediators of outcome. In addition, for the hypotheses about behavioral indicators (e.g., Behavioral Intentions Scales and likelihood of requesting information), PSQ ratings will be examined as potential mediators of outcome. These analyses will be conducted to observe trends and highlight directions for further research.

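### The protocol disagrees with itself on how many texts each arm shows; if it is one fixed text or bundle per arm, the comparison holds only for those texts and the readability adjustment cannot be estimated

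*Protocol article*

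**What the plan says.** Data collection and measures describes the exposure step in one sentence: "Parents will then be presented with one of two descriptions of EBP, depending on their random assignment". Read literally, this is one text per condition.

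The Randomization section, which defines the conditions, uses the plural in both arms. For marketing: "Parents in the marketing condition will be presented with the descriptions of EBP that were rated as most appealing in Phase 2". For control: "parents in the standard information condition will review descriptions of EBP created for parents by leading scientific organizations in our field", followed by three organisations given as examples and one excerpt offered as a sample. The one stated control on text features is: "Messages will be balanced to ensure comparable number of words".

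The Outcomes section adds that, if the basic comparisons show group differences, regression models will adjust for several variables, among them "readability statistics generated on the messages".

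The target of inference is a class of messages. Phase 3 is meant to "evaluate the effectiveness of targeted marketing versus standard clinical information". Specific aims and study phases and the article's Discussion word the hypotheses at the same level. The Discussion part of the abstract says the study will show "whether a well-established marketing framework and measurement approach can be used to increase demand for EBP among parents of ASUDs". Sample size and power describes the aim more modestly, as proof of concept.

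**The concern.** The text is the intervention here, so the number of texts and the way a parent comes to see a particular one are core design features. Two neighbouring sections describe them differently.

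The difference affects what can be concluded. With one text per arm, any peculiarity of that text, such as an awkward control paragraph or a striking marketing phrase, belongs entirely to the condition. The choice of which organisation's text serves as control could then influence the result, and matching word counts removes only one of many differences. Several texts in a fixed bundle, shown identically to everyone in the arm, do not help: that is still one stimulus per arm. At stake are the reach of the conclusion and whether one of the planned analyses can be run.

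**Working it through.** **1. The plan's own figure.** Sample size and power gives 80 per group and power of 71%, 88% and 96% for effect sizes .4, .5 and .6. Alpha is not stated; two-sided 0.05 is assumed. Power = Φ(d·√(80/2) − 1.96):

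- d = .4: 2.530 − 1.960 = 0.570, power 71.6%
- d = .5: 3.162 − 1.960 = 1.202, power 88.5%
- d = .6: 3.795 − 1.960 = 1.835, power 96.7%

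The noncentral t gives 71.0%, 88.2% and 96.5%. The stated figures reproduce. They count variation between parents only, so they are the power to detect a difference between the texts actually shown.

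**2. Readability under one text or bundle per arm.** Readability is a property of the text, not of the parent. With a fixed stimulus per arm it takes one value in each arm, so it is a linear function of the arm indicator. The design matrix with intercept, arm and readability then has rank 2, not 3, and the adjusted group effect has no unique estimate. This result needs no assumed figure.

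**3. Class-level error, illustration only.** Let τ be the SD between texts of the same class, in units of d. The protocol gives no value; τ = 0.1 to 0.2 is assumed. Let k be the number of texts per arm, with each parent seeing one. The sampling variance of d is 2/80 = 0.025 (SE 0.158).

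- Both arms' texts treated as random: SE = √(0.025 + 2τ²/k)
- Only the control text treated as random: SE = √(0.025 + τ²/k)
- False-claim rate of an analysis that ignores text: 2·(1 − Φ(1.96 × 0.158/SE))

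| Setting | τ | SE | False-claim rate |
|---|---|---|---|
| k = 1, control only | 0.1 | √0.035 = 0.187 | 9.8% |
| k = 1, control only | 0.2 | √0.065 = 0.255 | 22.4% |
| k = 1, both | 0.1 | √0.045 = 0.212 | 14.4% |
| k = 1, both | 0.2 | √0.105 = 0.324 | 33.9% |
| k = 3, both | 0.1 | √0.0317 = 0.178 | 8.2% |
| k = 3, both | 0.2 | √0.0517 = 0.227 | 17.3% |

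With a smaller τ of 0.05 and k = 1, the rates are 6.2% (control only) and 7.4% (both).

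**4. What a text-level test could do.** With k texts per arm it has 2k − 2 degrees of freedom, hence none at k = 1. If the text accounts for an assumed 1% to 10% of outcome variance, text-level power at d = .5 is about 68% down to 35% with four texts per arm, and about 80% down to 57% with eight. The stated parent-level power at that effect size is 88%.

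**The case against.** The strongest reply is that the single-text reading rests on one clause. The section that defines the conditions uses the plural in both arms, the hypotheses speak of messages, and a readability adjustment makes sense only if readability varies within an arm. The clause may be shorthand for two sets, and an article may leave the exact stimuli to the full protocol. This stands in part. A reader might infer that the trial is committed to one text per arm, and the document does not establish that. But the two sections differ as written, and the plural alone does not say that texts vary between parents.

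Second, a reader might infer that oddities of a text would be invisible in the data. They would not be. Parents rate the presented information on relevance, appeal, believability, ease of understanding and amount, and these ratings are examined as possible mediators. The marketing messages are also tested beforehand in cognitive interviews. These steps help to describe a text effect; they do not separate it from the condition.

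Third, a reader might take 14–34% as the trial's error rate. Nothing in the document supports any value of τ. The marketing text is also not a random draw: Phase 2 parents' preferences select it, so selection is part of the intervention. That is why the control-only figures are shown too.

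Fourth, a reader might infer that the trial could not support its conclusion at all. The abstract asks whether the framework can be used to raise demand, and the stated ambition is proof of concept. One marketing text beating one standard text is relevant evidence for that. It falls short only of the class-level hypotheses.

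**Conclusion.** The inconsistency is real and should be resolved. The consequences are conditional: they follow if every parent in an arm sees the same text or the same bundle. In that case the randomised comparison remains valid for those texts, but it does not separately support claims about targeted marketing versus standard clinical information as classes, and the readability-adjusted group effect cannot be estimated. The collinearity is exact.

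The size of the class-level error depends on the assumed between-text SD and on which arms' texts are treated as random. For an SD of 0.1 to 0.2 in d and one text per arm, it is roughly 10–22% (control only) or 14–34% (both), against a nominal 5%. The direction does not depend on the assumption; the magnitude does.

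**What to change.** Reconcile Randomization with Data collection and measures by stating how many texts each arm has and how a parent is assigned to one.

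**Preferred.** Within each arm, let the survey software randomly show one of several word-matched texts, or one of several sets if each parent is meant to read more than one. Take control texts from the organisations already named and marketing texts from the top-ranked Phase 2 messages. Record the text shown. Report the arm effect averaged over texts, with the spread between texts. Readability then varies within an arm, although only a few texts inform its coefficient.

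**Alternative.** Keep one text or bundle per arm, limit the conclusion to those texts as proof of concept, and drop the readability adjustment.

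**Cost.** The preferred option needs a within-arm randomiser and a few extra short texts (with three per arm, 2 × 3 − 2 = 4 more) and no extra participants. Lower-ranked marketing messages may be slightly less appealing than the first. A few texts per arm reduce the problem without removing it (about 8–17% with three, under the same assumptions), and a text-level test would have low power, so the spread between texts is best reported descriptively. The alternative costs only wording and one planned covariate.

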### Benefits of measuring perceived service quality

Prior marketing studies have demonstrated three major advantages of using measures like the SERVQUAL to evaluate PSQ. First, use of PSQ measures can establish the service quality attributes that most strongly predict behavioral intentions with regard to service selection and loyalty [33,37]. Such knowledge can potentially be used to develop targeted marketing messages to increase customer demand for new services and to devise concrete strategies to increase customer satisfaction [30]. Second, repeated administration of PSQ instruments can be used to evaluate whether specific marketing initiatives are effective in changing customers’ opinions of service [26,30]. Finally, service providers can periodically use a PSQ questionnaire to ensure that customers receive consistent, high-quality service, which can then be used to support specific marketing claims [26].

To date, PSQ measures have been used to evaluate health services in a range of settings across multiple countries, including nursing homes, hospitals, outpatient medical clinics, and dental clinics [44-50]. However, only one prior study has used a PSQ questionnaire to evaluate mental health services [50], and no studies have used one to evaluate SUD services. Moreover, an examination of prior studies reveal a number of modifications to extant PSQ questionnaires to increase their relevance to health services. Focusing on the SERVQUAL, modifications in prior health-care studies in the United States have included removing items [45,50], revising items [45,49,50], and adding new items [49,51]. These modifications have been associated with changes to the SERVQUAL’s psychometric properties and structure, with some studies finding that the SERVQUAL had three or four dimensions [52] and others finding six or more dimensions [49,51,53]. New quality dimensions found in more than one study have included “caring”, “empathy”, and “provider competence”.

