### Survey analysis

Descriptive statistics will be generated to summarize responses for the market research questions. Additional analyses will be conducted to test the psychometric properties of the new PSQ, including its factor structure, internal consistency, and validity (criterion, convergent, and discriminant). Items with a high proportion of missing data will be eliminated to create a more parsimonious scale. The following analyses are planned: *Factor Structure*. The target sample of 400 and expected questionnaire length of 20 items will enable analyses to be conducted using both Exploratory Factor Analysis (EFA) and Confirmatory Factor Analysis (CFA). EFA will be conducted using principal component analysis as the extraction method and promax as the rotation method. CFA will be conducted to further assess the scale’s structure. Model fit will be evaluated using conventional-fit indices, including RMSEA, CFI, and chi-square [78]. *Reliability*. Internal consistency for each scale will be calculated using Cronbach’s alpha, with values exceeding .7 viewed as evidence of high internal consistency [79]. *Criterion Validity*. Consistent with the initial SERVQUAL validation [39], criterion validity will be tested using global assessments of service expectations on a 10-point scale (1 = poor, 10 = excellent). *Convergent Validity*. Loading of scale items on their corresponding factors will be examined to assess convergent validity. *Discriminant Validity*. Discriminant validity will be tested by constraining each correlation between pairs of factors (one at a time) to unity in the measurement model and repeating the CFA. If the constrained CFA increases chi-square, it will support the distinctiveness of each scale’s component dimensions.

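### Hypothesis 1 is tested by an unadjusted, post-message comparison, and baseline covariates enter only after a difference is found, so they cannot help to detect one

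*Protocol article*

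**What the plan says.** Hypothesis 1 (Specific aims and study phases) is that parents shown targeted marketing will give higher PSQ ratings than parents shown standard clinical information. Procedures: study phase 3 describes the comparison of the two conditions "in increasing parent impressions of PSQ".

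Under Data collection and measures, the Phase 3 baseline holds the core measures plus questions on parents' attitudes to EBP, their awareness of it, earlier use and intention to use it. After the message and some ratings of it, "Parents will then complete the PSQ measure and a Behavioral Intentions Scale". No PSQ or other quality rating is listed before the message.

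Under Outcomes, hypothesis 1 is tested by comparing means. Regression on pre-message variables follows only where that basic comparison has shown a group difference. The covariates are given as examples and include EBP attitudes, awareness and intentions.

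Sample size and power states that "The target sample of 160 (n = 80 per group) will provide 71 percent power to detect an ES of .4", then "88 percent for an ES of .5; and 96 percent for an ES of .6".

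Two other places bear on the point. Benefits of measuring perceived service quality remarks that "repeated administration of PSQ instruments can be used to evaluate whether specific marketing initiatives are effective in changing" customers' opinions. Survey analysis plans, for criterion validity in Phase 2, "global assessments of service expectations on a 10-point scale (1 = poor, 10 = excellent".

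**The concern.** A baseline covariate in a randomized comparison earns its place by removing outcome variance from the test of the treatment effect. The plan collects plausible covariates for PSQ before the message but keeps them for a follow-up regression that is run only once the unadjusted test has found a difference. In that role they can confirm or weaken a positive result. They cannot turn a missed effect into a detected one.

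This matters because the margin is thin. The sample is fixed at 160, stated power is 71% at an effect size of .4, and the earlier effects that the protocol cites are .20, .26 and .30. Covariate adjustment is one of the few ways left to gain precision. The baseline also has a counterpart for the intentions outcome (intent to use) but no direct counterpart for PSQ, so a short quality rating is a natural further candidate.

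**Working it through.** **Inputs**

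- 80 per group; effect sizes .4, .5 and .6 with powers 71%, 88% and 96% (Sample size and power).
- Significance level: not stated. Two-sided 0.05 is inferred because it reproduces all three powers; one-sided 0.05 gives 81%, 93% and 98%.
- Missing data: none assumed. No dropout rate is given, and baseline, message and PSQ are described as one sequence.
- R, the correlation of the baseline covariates taken together with post-message PSQ: not in the protocol. Assumed, .2 to .6.

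**Step 1: the plan's own figures.** Power is the chance that a noncentral t with 158 degrees of freedom and noncentrality λ = d × √(n/2) exceeds the two-sided critical value. With n = 80, √40 = 6.325.

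- d = .4: λ = 2.530, power 71.0% (stated 71%)
- d = .5: λ = 3.162, power 88.2% (stated 88%)
- d = .6: λ = 3.795, power 96.5% (stated 96%)

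The stated powers are those of an unadjusted two-sample comparison. They take no credit for any covariate.

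**Step 2: the conditional regression.** It is run only after the unadjusted comparison has shown a difference. The chance of finding an effect by this route is therefore at most that of the unadjusted test, 71.0% at d = .4, whatever R is.

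**Step 3: adjustment in the main test.** Analysis of covariance reduces the residual SD by the factor √(1 − R²), so λ = d × √(n/2) / √(1 − R²). For example, with d = .4 and R = .5, λ = 2.530 / √.75 = 2.921. The last column is 80/(1 − R²).

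| R (assumed) | λ at .4 | Power, ES .3 | Power, ES .4 | Power, ES .5 | Equivalent n per group |
|---|---|---|---|---|---|
| none | 2.530 | 47.0% | 71.0% | 88.2% | 80.0 |
| .2 | 2.582 | 48.6% | 72.8% | 89.4% | 83.3 |
| .3 | 2.652 | 50.7% | 75.0% | 90.9% | 87.9 |
| .4 | 2.760 | 53.9% | 78.3% | 92.9% | 95.2 |
| .5 | 2.921 | 58.6% | 82.7% | 95.2% | 106.7 |
| .6 | 3.162 | 65.4% | 88.2% | 97.5% | 125.0 |

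The table uses 157 degrees of freedom for the adjusted rows. Spending two or three more on extra covariates leaves the entries for R = .3 to .6 unchanged to one decimal.

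The effect size detectable with 80% power (normal approximation) is (1.960 + 0.842) × √(2/80) × √(1 − R²): .443 with no covariate, .423 at R = .3, .384 at R = .5 and .354 at R = .6.

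**Step 4: what a new baseline rating adds by itself.** The right comparison is with a model that already holds the attitude, awareness and intent items. At ES .4:

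- R from .3 to .5: 75.0% to 82.7%, a gain of 7.7 points
- R from .4 to .5: 78.3% to 82.7%, a gain of 4.4 points

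**The case against.** The strongest reply is that nothing here is wrong. Hypothesis 1 is a between-group contrast, the Outcomes section tests that contrast, and randomization makes it unbiased without a pre-test. The protocol calls the study proof of concept and the sample adequate for a medium effect, with 88% power at .5. All of this stands, and it limits the point to precision.

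A reader might infer a contradiction from the Background remark on repeated PSQ administration. The text does not support that. The remark reports what PSQ measures can be used for in marketing research; it is one of three listed advantages and does not commit Phase 3 to a pre-test. Nor does the wording about increasing impressions imply change within a parent, since it is tied to marketing versus standard information.

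A reader might also infer that one ready-made item would restore the power. That fails for three reasons. An added item does nothing while the main test stays unadjusted. Survey analysis speaks of global assessments in the plural and of service expectations, so a Phase 3 item would be an adaptation. And Phase 2 is a single survey, so it can give only a same-occasion correlation with the PSQ. Power depends on the correlation of a pre-message rating with PSQ after the message, which could be lower.

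Priming is a fair objection too: a quality rating shortly before the PSQ could anchor answers in both arms. The risk is untested but probably small, because the session already asks about intent before the message and intentions after it.

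Finally, a condensed article may leave covariate choice to an analysis plan. It may, but this one does state the order of analyses, and that order is the weakness.

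**Conclusion.** The point holds as one of precision, not validity. As described, the test of hypothesis 1 has 71% power at an effect size of .4, and the planned use of baseline covariates cannot raise it. Adjusting in the main test would raise it to between about 73% and 88% for an assumed R of .2 to .6. The gain is only 2 to 4 points at R = .2 to .3 and reaches about 12 points at R = .5. At the health-care effect size of .30 that the protocol cites, power stays low even so: 47% unadjusted and about 59% at R = .5.

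The main benefit comes from changing the model. A new baseline rating is a secondary improvement, worth roughly 4 to 8 points in the two examples worked. All of these figures rest on a two-sided 0.05 test, no missing PSQ data and correlations that the protocol does not supply. This is a desirable improvement, not a necessary correction.

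**What to change.** 1. Prespecify the main test of hypothesis 1 as an analysis of covariance of post-message PSQ on arm, adjusted for the pre-message EBP attitude, awareness and intent items, and run it whatever the unadjusted comparison shows. Keep the unadjusted means as a supporting description. Limit the covariates to parent measures taken before the message; the readability statistics that Outcomes also lists describe the message shown, not the parent. Cost: a sentence or two in the analysis text and no new data.

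2. Optionally, add one 10-point global service-quality rating to the Phase 3 baseline, adapted from the Phase 2 global assessments, and name it as a further covariate. It would also show where parents started. Cost: one question and a small, untested risk of priming or anchoring the PSQ in both arms.

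3. If power is restated for the adjusted test, show it over a range of correlations and say that they are assumed. A concurrent correlation from Phase 2 can guide the choice of item but should not be entered as the pre-to-post-message value.
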